## Part E: Foot care outcome expectation

After reading each statement, please tick ( ✓ ) under the description that best describes how **CONFIDENT** you are about undertaking yourself each of the following foot-care tasks. Please answer **about your CONFIDENCE to do the foot care, not about what you actually do.**

| When I perform good foot self-care behaviour, I become more confident that I can        | Strongly disagree |   |   |   | Strongly agree |
|-----------------------------------------------------------------------------------------|--------------------------|---|---|---|-----------------------|
| 1. protect my feet from injury                                                          | 1                        | 2 | 3 | 4 | 5                     |
| 2. look at my feet daily to check for cuts, scratches, blisters, redness or dryness     | 1                        | 2 | 3 | 4 | 5                     |
| 3. keep hygiene of my foot/ feet                                                        | 1                        | 2 | 3 | 4 | 5                     |
| 4. keep my toes always dry                                                              | 1                        | 2 | 3 | 4 | 5                     |
| 5. Keep my feet/ foot not dry (by putting lotion when my skin is dry)                   | 1                        | 2 | 3 | 4 | 5                     |
| 6. judge when my foot needs appropriate treatment by a doctor/ nurse/ medical assistant | 1                        | 2 | 3 | 4 | 5                     |

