### **1.6.3 Foot care outcome expectation**

Foot care outcome expectation in this study can be defined on self-belief (level of confidence) that a foot behaviour will have the desired effect.

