### 2.4.1 Self-efficacy; definition and description

The American psychologist, Albert Bandura in 1977, first introduced the concept of self-efficacy developed from social cognitive theory, formerly known as social learning theory (Bandura, 1994). By means that a central ideology of social cognitive theory is the concept of self-efficacy.

Self-efficacy defined as individuals' beliefs about their capabilities to produce designated levels of performance that activity influence over events that affect their lives (Bandura, 1994). Self-efficacy theory is a behaviour specific and dynamic, because it focuses on beliefs about individual abilities in a particular activities (Bandura, 1994; 1997; Wu et al., 2007). The patient's self-efficacy may affect behavioural choices and subsequent outcomes (Adam & Folds, 2014). This description shows that people's self-efficacy is not of a general nature, but related to a specific situations and easy to influence characteristic that is strictly situation-and task-related (Lenz & Shortridge-Baggett, 2002). For example; individuals can judge themselves as being very competent in a specific area and less competent in another area. It means that this concept emphasizes not individuals' skills, but their judgment of what they believe they can do. Judgment about the specific task built on past experiences will vary according to multiple factors such as strength and beliefs.

The basic premise underlying self-efficacy theory is that the expectations of personal mastery (self-efficacy or efficacy expectation) and success (outcome expectation) determine whether an individual will engage in particular behaviour (Figure 2.2). Self-efficacy (efficacy expectation) concerns the confidence in one's capability to produce the behaviour. An outcome expectation is a person's belief about the outcomes result from a given behaviour. These outcomes can take the form of physical, social and self-evaluative effects (Lenz & Shortridge-Baggett, 2002). The distinction between outcome and efficacy expectations is important because both are required for behaviour.

[figure not shown]

Figure 2.2 The relationship between efficacy expectation and outcome expectation source Bandura, (1977); Shortridge-Bagett & van der Bijl, (1996)

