## Part D: Foot care self-efficacy (efficacy expectation)

After reading each statement, please tick ( ✓ ) under the description that best describes how CONFIDENT you are about undertaking yourself each of the following foot-care tasks. Please answer **about your CONFIDENCE to do the foot care, not about what you actually do.**

|                                                                                                                          | Strongly
not
confident |  |  | Strongly
confident |
|--------------------------------------------------------------------------------------------------------------------------|------------------------------|--|--|-----------------------|
| 1. I can protect my feet                                                                                                 |                              |  |  |                       |
| 2. Even without pain/discomfort, I can look at my feet daily to check for cuts, scratches, blisters, redness or dryness. |                              |  |  |                       |
| 3. After washing my feet, I can dry between my toes.                                                                     |                              |  |  |                       |
| 4. I can judge when my toenails need to be trimmed by a podiatrist                                                       |                              |  |  |                       |
| 5. I can trim my toenails straight across                                                                                |                              |  |  |                       |
| 6. I can figure out when to use a pumice stone to smooth corns and/or calluses on my feet.                               |                              |  |  |                       |
| 7. I can test the temperature of the water before putting my feet into it.                                               |                              |  |  |                       |
| 8. If I was told to do so, I can wear shoes and socks every time I walk (includes walking indoor).                       |                              |  |  |                       |
| 9. When I go shopping for new shoes, I can choose shoes that are good for my feet.                                       |                              |  |  |                       |

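### The outcome expectation form (Part E) uses the self-efficacy instruction and a confidence stem, so its result could not be cleanly told apart from self-efficacy

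*Combined protocol and SAP*

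**What the plan says.** Section 1.6.3 defines foot care outcome expectation as "self-belief (level of confidence) that a foot behaviour will have the desired effect". Section 2.4.1 describes it as a "belief about the outcomes result from a given behaviour" and adds: "The distinction between outcome and efficacy expectations is important because both are required for behaviour". Section 2.6 gives an example in which believing that foot care benefits the feet is outcome expectation, and believing oneself capable of it is efficacy expectation. Section 3.6.1 (Section E) gives the FCOE score the same meaning as 1.6.3. It also asks that the content focus on foot complications, risk factors and foot care.

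FCOE and FCCS are separate secondary outcomes in 2.6 and 3.10, and both appear in specific objectives 1, 3 and 4 (section 1.5.2).

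The Part E form tells respondents to rate how confident "you are about undertaking yourself each of the following foot-care tasks" and to answer "about your CONFIDENCE to do the foot care, not about what you actually do". Part D, the self-efficacy form, carries the same two sentences. The Part E stem is "When I perform good foot self-care behaviour, I become more confident that I can", followed by six items scored 1 to 5 from disagree to agree.

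**The concern.** The definition concerns what foot care achieves. The instruction concerns whether the respondent can carry it out, which the protocol assigns to efficacy expectation. A respondent who follows the printed instruction is steered towards the Part D question.

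What is at stake is how one secondary outcome is read. If FCOE rises in the intervention group, the report would present it as an effect on the second half of the theory. With this form, the rise could partly or wholly reflect the confidence already captured by FCCS, and nothing in the stated plan would show how much. The data cannot be repaired once collected.

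**Working it through.** **Inputs.** Section 3.6.1 gives FCCS 12 items and FCOE 6. Counting the printed forms reproduces both figures.

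**Instruction.** Parts D and E share both sentences, so the instruction does not separate the constructs.

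**Stem.** Part D has no conditional clause. Part E begins with performing the behaviour, which points towards a consequence, but the consequence it names is confidence in what one can do.

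**Items.** Each Part E item set against its nearest Part D item:

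| Part E | Nearest in Part D | Match | Can be read as |
|---|---|---|---|
| E1 protecting feet against injury | D1 | paraphrase; injury is added | task or result |
| E2 daily inspection | D2 | nearly verbatim: "I can look at my feet daily to check for cuts, scratches, blisters, redness or dryness" in Part D | task |
| E3 foot hygiene | none | new | task or state |
| E4 toes kept dry | D3 drying between toes | topic only | task or state |
| E5 skin kept from drying, using lotion | D12 applying lotion | topic only | task or state |
| E6 judging when treatment is needed | D4 judging when nails need a podiatrist | parallel wording, different task | task |

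- Topic overlap: E1, E2, E4, E5, E6 = 5 of 6.
- Nearly verbatim: E2 = 1 of 6. No counterpart: E3 = 1 of 6.
- Plain tasks: E2, E6 = 2 of 6. Readable as a state or result: E1, E3, E4, E5 = 4 of 6.
- Part D items not matched: 12 − 5 = 7.
- Items naming infection, ulcer or amputation: 0 of 6. E1, with injury, comes closest.

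A text-similarity ratio (0 to 1) on the item wording gives 1.00 for E2–D2 once the opening clause of D2 is set aside, 0.62 for E1–D1 and 0.58 for E6–D4. It does not pick out D3 for E4 or D12 for E5, so those two matches rest on content alone.

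**Planned checks.**
- The content validity ratio in 3.6.2.1 asks experts whether each item is essential to its construct. It could expose a misplaced item, but it judges items rather than the instruction and stem. The panel is not told to compare FCOE with FCCS.
- Cronbach's alpha tests internal consistency. Six items that all reflect confidence could pass it.
- Principal component analysis is described in 3.6.2.1 and 3.9. Neither says that the two item sets are analysed together, and Table 3.5 lists factor analysis separately for each scale.

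No discriminant check is therefore stated.

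**Reach.** The FCOE score can range from 6 × 1 = 6 to 6 × 5 = 30. The sample size in 3.5.2 uses means of 32.32 and 36.22, which lie above 30, so it does not rest on FCOE. The primary outcome, foot self-care behaviour, is measured in Part C.

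**The case against.** The best defence starts from the whole stem. It asks what performing foot care leads to, and Part D asks nothing of that kind. Section 2.4.1 counts self-evaluative effects among possible outcomes, and gaining confidence from a behaviour can be seen as one. The protocol's own definition is phrased through confidence, so that word in Part E is not in itself a contradiction. The response anchors differ between the forms, and four of the six items can be read as a state or result.

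The form is also a draft. Section 3.7.1 sends it to six content experts and a pilot, and then to a second draft.

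Much of this stands. Part E is a hybrid, not a copy of Part D, and most of the overlap is of topic. What the defence does not remove is the instruction, which directs the answer to confidence in doing the tasks, or the absence of a stated check against FCCS. The planned review makes the correction easy but does not ensure that it happens.

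**Conclusion.** The point holds in a limited form. Part E conflicts with the protocol's definition in its instruction, in the consequence its stem names, and in at least two of its six items. An FCOE effect could not be cleanly interpreted as distinct from an FCCS effect. This affects one of four secondary outcomes. The change should be made, but it does not threaten the main comparison.

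A reader might infer that the trial measures self-efficacy twice, or that it cannot address outcome expectation at all. The documents do not show this: only one item is nearly verbatim, the stem is conditional, and how far the two scores coincide is an empirical matter. Nor do they show that a resident who thinks foot care useless would score high on FCOE. Such a person could reasonably disagree that performing it makes them more confident of avoiding injury.

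The conclusion rests on respondents taking the printed instruction at face value, and on the content matching above, which is a judgement for E4 and E5.

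**What to change.** Before the expert review, translation and pilot:

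1. Replace the Part E instruction and stem with wording about expected results, for example a stem such as *If I look after my feet every day, I expect that…*. Keep the 1–5 disagree–agree scale.
2. Recast at least E2 and E6 as expected results. Review E1, E3, E4 and E5 so that each states a result and not an ability.
3. Word the new items as personal expectations. Part F already tests knowledge about infection and foot ulcer, and close repeats would replace overlap with self-efficacy by overlap with knowledge.
4. Give the expert panel the 1.6.3 definition and ask whether each item belongs to outcome or efficacy expectation.
5. Check in the pilot that FCOE separates from FCCS, for example by the correlation between the scales or a joint principal component analysis of all 12 + 6 = 18 items.

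Pilot size limits step 5. Section 3.7.1 sets the pilot at 10% of the required sample, 0.10 × 142 ≈ 14 people, while the Appendix 6 budget prints pilot questionnaires for 50. With 14 respondents, a correlation matrix of 18 items has rank at most 13, so a joint component analysis would not be usable. In that case, report the inter-scale correlation with its interval from the pilot, and run the joint analysis on the main-study baseline data.

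The cost is redrafting an instruction, a stem and a few items before validation. The scale is being developed for this study, so comparability with published FCOE scores is not lost.

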### Part F: Knowledge on foot care

The questions below ask about your knowledge on foot care. Please **circle** in an appropriate answer.

| People with diabetes should.....                                                       | Answer |       |            | Remark |
|----------------------------------------------------------------------------------------|---------------|-------|------------|---------------|
| 1. take medication regularly because they liable to get diabetes complication          | True          | False | Don't know |               |
| 1. look after their feet because they are more liable to get infection (true)          | True          | False | Don't know |               |
| 2. look after their feet because they may not feel a minor injury to their feet (true) | True          | False | Don't know |               |
| 3. look after their feet because wounds and infection may not heal quickly (true)      | True          | False | Don't know |               |
| 4. look after their feet because they may get a foot ulcer (true)                      | True          | False | Don't know |               |
| 5. not smoke because smoking causes poor circulation affecting the feet (true)         | True          | False | Don't know |               |
| 6. check their feet daily (true)                                                       | True          | False | Don't know |               |
| 7. treat themselves if they found redness/ bleeding between their toes (false).        | True          | False | Don't know |               |
| 8. Tell doctor if they have corn/ hard skin lesion                                     | True          | False | Don't know |               |
| 9. wash their feet daily (true)                                                        | True          | False | Don't know |               |
| 10. check temperature of the water before wash their feet to avoid injury (true)       | True          | False | Don't know |               |
| 11. check inside of their shoes only when necessary (false)                            | True          | False | Don't know |               |

### Part G: Quality of life

These questions ask about the effect your **FOOT PROBLEMS** may have on your daily life and well-being. By **foot problems** we mean **lost or reduced feeling** in your extremities, **pain, discomfort** and/or **ulcers (open sores) on your feet** and, in some cases **unsteadiness** while walking or standing. Please note that many **questions have three parts**. Answer every question by filling in the blank or ticking one box for each part tick (✓) two boxes per line). Please make sure you answer all questions. Please concentrate on how you have felt **IN THE PAST 4 WEEKS** for all of the questions.

| In the past 4 weeks how often have you experienced the following symptoms?                   | All the time | Some time | Never | How much bother did this cause you? |             |      |
|----------------------------------------------------------------------------------------------|--------------|-----------|-------|-------------------------------------|-------------|------|
|                                                                                              |              |           |       | Very much                           | Some bother | None |
| 1. Burning in your legs or feet                                                              |              |           |       |                                     |             |      |
| 2. Excessive heat or cold in your legs or feet                                               |              |           |       |                                     |             |      |
| 3. Pins and needles in your legs or feet                                                     |              |           |       |                                     |             |      |
| 4. Shooting or stabbing pain in your legs or feet                                            |              |           |       |                                     |             |      |
| 5. Throbbing in your legs or feet                                                            |              |           |       |                                     |             |      |
| 6. Sensations in your legs or feet that make them jump                                       |              |           |       |                                     |             |      |
| 7. Irritation of the skin caused by something touching your feet, such as bedsheets or socks |              |           |       |                                     |             |      |

| In the past 4 weeks how often have you experienced the | All the time | Some time | Never | How much bother did this cause you? |
|--------------------------------------------------------|--------------|-----------|-------|-------------------------------------|
|--------------------------------------------------------|--------------|-----------|-------|-------------------------------------|

| following symptoms?                                              |  |  |  | Very much | Some bother | None |
|-------------------------------------------------------------------------|--|--|--|-----------|-------------|------|
| 8. Numbness in your feet                                                |  |  |  |           |             |      |
| 9. Inability to feel the difference between hot and cold with your feet |  |  |  |           |             |      |
| 10. Inability to feel objects with your feet                            |  |  |  |           |             |      |

| In the past 4 weeks how often have you experienced the following symptoms? | All the time | Some time | Never | How much bother did this cause you? |             |      |
|-----------------------------------------------------------------------------------|--------------|-----------|-------|--------------------------------------------|-------------|------|
|                                                                                   |              |           |       | Very much                                  | Some bother | None |
| 11. Weakness in your feet                                                         |              |           |       |                                            |             |      |
| 12. Problems with balance or unsteadiness while walking                           |              |           |       |                                            |             |      |
| 13. Problems with balance or unsteadiness while standing                          |              |           |       |                                            |             |      |

The following questions ask about how your FOOT PROBLEMS affect your daily activities, relationships and feelings.

|                                     |     |    |                                                                                   |
|-------------------------------------|-----|----|-----------------------------------------------------------------------------------|
| Are you in PAID WORK? | Yes | No | If YES please go to Question 14.
If NO please go to Question 15. |
|-------------------------------------|-----|----|-----------------------------------------------------------------------------------|

| In the past 4 weeks, HOW MUCH have your foot problems interfered with your: | Very much | Some what | Not at all | How important is this aspect of your life to you? |           |            |
|------------------------------------------------------------------------------------|-----------|-----------|------------|---------------------------------------------------|-----------|------------|
|                                                                                    |           |           |            | Very much                                         | Some what | Not at all |
| 14. Ability to perform your paid work?                                             |           |           |            |                                                   |           |            |
| 15. Ability to perform tasks around the house or garden?                           |           |           |            |                                                   |           |            |
| 16. Ability to take part in leisure activities?                                    |           |           |            |                                                   |           |            |

| In the past 4 weeks:                                                                                                             |           |           |            | How important is this aspect of your life to you? |           |            |
|----------------------------------------------------------------------------------------------------------------------------------|-----------|-----------|------------|---------------------------------------------------|-----------|------------|
|                                                                                                                                  | Very much | Some what | Not at all | Very much                                         | Some what | Not at all |
| 17. How much has your foot problems interfered with your relationships with people close to you?                                 |           |           |            |                                                   |           |            |
| 18. Have you felt more physically dependent than you would like to be on people close to you as a result of your foot problems?  |           |           |            |                                                   |           |            |
| 19. Have you felt more emotionally dependent than you would like to be on people close to you as a result of your foot problems? |           |           |            |                                                   |           |            |
| 20. Has your role in the family changed as a result of your foot problems?                                                       |           |           |            |                                                   |           |            |

|  |                                            |
|--|--------------------------------------------|
|  | How much bother did this cause you? |
|--|--------------------------------------------|

| How much do you agree with the following statements:                               | Agree | Neither agree or disagree | Disagree | Very much | Some bother | None |
|------------------------------------------------------------------------------------|-------|---------------------------|----------|-----------|-------------|------|
| 21. People treat me differently from other people as a result of my foot problems. |       |                           |          |           |             |      |
| 22. I feel older than my years as a result of my foot problems.                    |       |                           |          |           |             |      |
| 23. My self - confidence is affected as a result of my foot problems.              |       |                           |          |           |             |      |
| 24. My foot problems make my life a struggle.                                      |       |                           |          |           |             |      |
| 25. I generally feel frustrated because of my foot problems.                       |       |                           |          |           |             |      |
| 26. My foot problems cause me embarrassment.                                       |       |                           |          |           |             |      |
| 27. I feel depressed because of my foot problems                                   |       |                           |          |           |             |      |

